### Intervention

The “Shoupa” app is an efficient medical and health service platform that can record patients' medications in real-time, aiming to manage PD better. The “Shoupa” app modules contain six sessions, prescription management, medication recording, effect recording, adverse report, patient's diary, and exploratory research. Persons with PD can easily submit their condition through the “Shoupa” app, and the professional triage consultant will arrange the most appropriate doctor to answer the question. In the “effect recording” section, patients can automatically generate historical reports based on the medication effect records and can conveniently customize historical reports through the date range. The “patient's diary” section provides a professional record template, and users can update their diary daily to control their physical state. The “medication recording” section provides users with convenient and intuitive medication reminders. Users can add medication records, set reminders based on prescriptions, and/or record each medication's effects. Besides, in the “exploratory research” part, the developer inserts oriented rehabilitation training videos (Tai Chi training) as needed to realize rehabilitation under the home condition. The “Shoupa” app software has been released as iPhone and Android apps.

During the recruitment process, all participants will see the registration screen of the application. However, after random assignment, participants will only be granted access to their assigned experimental group's features. To prevent interference between the control group, the basic experimental group, and the balanced-enhanced experimental group, participants will be instructed not to discuss their exercises during the experiment. A screenshot of the “Shoupa” app is shown in Figure 2.

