#### Control Group

Participants assigned to the control group will stay on the app's registration screen until the end of the 16-week study period. Therefore, they do not have the right to use any application functions that can help them improve their balance functions, so they will be encouraged to continue their daily activities.

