#### Basic Experimental Group

Subjects who participate in the basic experimental group will get the self-monitoring function of using the app for daily medication management, but the “exploratory research” part of the function is prohibited. Members of the patient research team will organize persons with PD or their families to download the “Shoupa” app. Besides, the patients will perform a normal daily routine. For more information, the “Shoupa” app is presented in Supplementary File 1.

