#### Balanced-Enhanced Experimental Group

Subjects participating in the balanced-enhanced experimental group are authorized to use the “exploratory research” function in addition to using the app for medication management. The “exploratory research” part is a set of simple Tai Chi training designed for persons with PD. The simple Tai Chi training is shown in Supplementary Figure 1. The training plan includes 60-min exercise classes, three times a week, for 16 weeks. Each session includes 40 min of the main training, 10 min of warm-up, and 10 min of finishing exercise. All exercises involve shifting the body's center of gravity (COG), as illustrated in Supplementary File 2. In addition to the therapist's guidance, each part of the app program contains a demo video and supporting subtitle text. The app program is connected to a website, and the clinician-side app can track the patient's training times through the website's background to monitor compliance with the plan. In other words, the “Shoupa” app records the training times the patient has watched the teaching course, but it is challenging to determine whether the patient is actually following the training. This requires the app to develop real-time video recording functions in future technological updates.

Every weekend during the intervention, the research team will arrange members to supervise and follow up on the participants to strengthen patients' compliance with home training. To confirm participant self-reported adherence to the study plan, patients' family members will be contacted through the phone to enquire weekly about patients' actual compliance. If participants experience dizziness, headache, or feel weak during the study, the intervention will be stopped immediately. After recovery, participants can therefore complete the interventions. If participants and their families need to consult any questions or have doubts during the study, they can always communicate with our team members. The research team will explain to the patients and their families in detail. Furthermore, the research team will count the participants who withdrew from the study and the reasons for the withdrawal.

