### Adverse Events

All adverse events reported during the study will be recorded on the case report form (CRF). For this trial, adverse events will be defined as any unfavorable and unexpected signs, symptoms, or diseases related to the intervention, such as falls, fractures, dizziness, and hypertension. Researchers will ask participants about the adverse events they experienced before training begins and will record all the intervention's adverse events. Participants will be phoned and asked weekly about any experienced adverse events. Subjects will also be required to report any adverse events throughout the study protocol spontaneously. A serious adverse event (SAE) will be notified to the principal investigator within 24 h. The principal investigator is responsible for managing the safety report. Any adverse events related to the intervention will be reported to the ethical review committee of the Shanghai University of Sport. Although this committee is from the same institution as the authors, the ethics committee membership is independent of the investigators. None of the investigators are members of the ethics committee.

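### Opportunities to report adverse events differ by arm, so any between-arm comparison of event counts is at risk of ascertainment bias

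*Protocol article*

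**What the plan says.** Two reporting routes are stated without restriction to an arm (protocol article, Adverse Events): "Participants will be phoned and asked weekly about any experienced adverse events" and "Subjects will also be required to report any adverse events throughout the study protocol spontaneously". The same section sends all reported events to the case report form.

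The other routes depend on the arm:

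- **App.** The Intervention section lists six modules: "prescription management, medication recording, effect recording, adverse report, patient's diary, and exploratory research". For controls, "Participants assigned to the control group will stay on the app's registration screen until the end of the 16-week study period". The basic arm has the self-monitoring functions, "but the “exploratory research” part of the function is prohibited". Tai Chi participants "are authorized to use the “exploratory research” function in addition to using the app for medication management".
- **Training-linked questioning.** The Adverse Events section says "Researchers will ask participants about the adverse events they experienced before training begins". Footnote a to Table 1 also ties the monitoring of adverse experiences to treatment sessions. Only the Tai Chi arm has training sessions.
- **Compliance contacts.** Under the Tai Chi arm only: "Every weekend during the intervention, the research team will arrange members to supervise and follow up on the participants", together with a weekly telephone enquiry to family members. The stated purpose of both is adherence.

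The Statistical Analysis section describes no between-arm test of adverse events.

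**The concern.** The number of events on a case report form depends on how many occur and on how many chances each has to be mentioned. If the second differs by arm, counts differ even when training causes no harm.

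The named examples of adverse events include falls and dizziness. In this trial a fall bears on harm and on benefit. Fuller detection in the Tai Chi arm could create an apparent excess of falls or hide a true reduction. The Discussion says the trial should show whether app-based Tai Chi ought to be advocated, and readers will look at events by arm when they judge that. If the source of each event is not recorded at the time, no later analysis can undo the imbalance.

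**Working it through.** **Step 1. Routes by arm during the 16-week intervention**

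| Route | Control | Basic | Tai Chi |
|---|---|---|---|
| Weekly call on adverse events | yes | yes | yes |
| Spontaneous report | yes | yes | yes |
| App adverse report module | no | yes, inferred | yes, inferred |
| Training-linked questioning | no | no | yes if repeated at sessions; no if asked once before the programme |
| Weekend and family contacts (for compliance) | not described | not described | yes, incidental |

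Explicit adverse event routes number 2 for control, 3 for basic, and 3 or 4 for Tai Chi, depending on how the pre-training sentence is read. The compliance contacts come on top as occasions on which an event might be mentioned. The ordering is Tai Chi ≥ basic > control.

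**Step 2. What this could do to a ratio**

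The plan gives no figure to reproduce and no capture rates, so all values here are assumptions. Let b be the probability that the shared routes capture an event, e the probability that one additional, independent route captures it, and k the number of additional routes.

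Probability recorded = 1 − (1 − b)(1 − e)^k

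With equal true risk, the apparent ratio against control is this probability divided by b. Here k = 1 is the app module alone (the basic arm, and also the Tai Chi arm if nothing else adds events). For Tai Chi, k = 2 or 3 means one or two routes beyond those of the basic arm.

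Example: b = 0.7, e = 0.5, k = 1 gives 1 − 0.3 × 0.5 = 0.85, and 0.85 / 0.70 = 1.21.

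| b | e | k = 1 | k = 2 | k = 3 |
|---|---|---|---|---|
| 0.5 | 0.1 | 1.10 | 1.19 | 1.27 |
| 0.5 | 0.3 | 1.30 | 1.51 | 1.66 |
| 0.5 | 0.5 | 1.50 | 1.75 | 1.88 |
| 0.7 | 0.1 | 1.04 | 1.08 | 1.12 |
| 0.7 | 0.3 | 1.13 | 1.22 | 1.28 |
| 0.7 | 0.5 | 1.21 | 1.32 | 1.38 |
| 0.9 | 0.1 | 1.01 | 1.02 | 1.03 |
| 0.9 | 0.3 | 1.03 | 1.06 | 1.07 |
| 0.9 | 0.5 | 1.06 | 1.08 | 1.10 |

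Tai Chi against basic, for k = 2 or 3 against k = 1, runs from 1.01 to 1.27. For example, at b = 0.5 and e = 0.3, 0.829 / 0.65 = 1.27. If Tai Chi adds nothing beyond the app, that ratio is 1.00. If app entries never reach the case report form either, k = 0 and the ratio against control is also 1.00.

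**Step 3. Masking**

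An apparent ratio is the true ratio multiplied by the detection ratio. At b = 0.7, e = 0.3, k = 2 the detection ratio is 1.22, so a true ratio of 1 / 1.22 = 0.82 would look like no difference.

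**The case against.** Several stronger readings are tempting, and the document does not support them.

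- **That the planned safety comparison is biased.** No such comparison is stated. Adverse events and falls are not listed as outcomes, and the Adverse Events section describes monitoring and reporting. What stands is the conditional statement: a comparison, if made, would be at risk.
- **That Tai Chi participants get 48 pre-training questions (3 sessions × 16 weeks).** The sentence can equally mean one question, before the programme, about earlier events. A question at every session also fits poorly with home training at times the patient chooses. Footnote a to Table 1 gives some support to session-linked collection but does not settle it. The gap between control and the app arms does not depend on this sentence.
- **That weekend and family contacts are safety queries.** Their stated purpose is compliance, and they may overlap. They are occasions for an event to come up and should not be counted as scheduled safety prompts.
- **That app entries demonstrably enter the same pool.** All reported events go on a paper case report form, but no passage says that app entries are transferred to it. Access to the adverse report module in the two app arms is inferred from what each is granted or barred from.

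It is also fair to say that call scripts and form fields are commonly left to the full protocol or the case report form. Their absence from an article is not the point here. The point is that the article itself fixes arm-dependent routes.

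Finally, an active weekly query for everyone limits the imbalance. If it is nearly complete, little is left for other routes to add.

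**Conclusion.** The concern holds as a risk to any between-arm comparison of adverse event counts, descriptive or formal. The unequal opportunity follows from the text: controls are without the app module, and training-linked questioning and compliance contacts fall on the Tai Chi arm. The likely direction is more recorded events in the Tai Chi arm.

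The size is unknown. It depends mainly on how completely the weekly call and spontaneous reports capture events, which the document does not give. Across the assumed values, Tai Chi against control ranges from 1.02 to 1.88 with one or two routes beyond basic, and from 1.01 to 1.50 if the app module is the only extra route. With 90% shared capture it is 1.10 or less throughout. These figures assume independent routes and equal true risk, and that events surfacing through the extra routes are recorded.

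A separate defect compounds this one. The Adverse Events section confines adverse events to those related to the intervention, a condition that an event in a control participant can hardly meet. Equal routes alone would not make the arms comparable, and a neutral definition alone would not equalise the routes.

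**What to change.** In the Adverse Events section:

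1. State that the weekly call uses the same scripted query and the same recall period in all three arms.
2. Record the source of each event on the case report form: weekly call, spontaneous report, app module, training-linked question, or compliance contact with participant or family.
3. Base any between-arm comparison on the routes common to all arms, namely the weekly call and spontaneous reports. Limiting it to the call alone would needlessly discard a shared route.
4. Report all serious adverse events by arm, whatever their source.
5. List events found only through the app module, training-linked questions or compliance contacts separately, without comparing their rates.
6. Clarify whether the question before training is asked once or before each session.
7. Address the relatedness condition in the definition as a separate change.

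For items 1 to 6 the cost is one extra field on the form, a few protocol sentences and a somewhat lower event count in the comparison. The calls are already planned. If the full protocol or the case report form already holds a script and a source field, only the statements on comparison and clarification remain to be added. The source field has to be in place before collection starts, since it cannot be reconstructed reliably afterwards.

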### Statistical Analysis

Data will be analyzed in an open computing environment, R language, version 3.5.2. Differences between groups of baseline variables will be tested using the chi-square test (categorical variable) and one-way analysis of variance (continuous variable). Repeated measure ANOVA will be used to compare the changes from baseline to 16 weeks among the control group, basic experimental group, and balanced-enhanced experimental group. Pairwise comparisons between the balanced-enhanced experimental group and the two other groups will be conducted only if the omnibus F-test statistics indicated that the null hypothesis should be rejected. An independent sample *t*-test (95% confidence interval) will be used to compare group means. Paired *t*-tests will be used to examine changes within the groups from baseline to 16 and 32 weeks.

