### Sample Size Calculation

Sample size calculations are based on the primary outcome measures of maximum excursion and directional control of limits of stability (LOS) measured using NeuroCom® Balance Master. Based on data provided by Li et al. (24), the primary outcome LOS was used to assess the maximum excursion and directional control in patients with PD (Cohen's *d* = 0.28, 15% improvement in maximum excursion, 12% improvement in directional control). For the current study, a similar effect size difference is anticipated between the balanced-enhanced experimental condition and the control condition. A smaller effect size difference is anticipated between the balanced-enhanced experimental condition and the basic experimental condition, hence the larger sample size. Based on sample size calculations (α = 0.05, β = 0.2), a total sample of 144 (assuming 15% attrition) will be sufficient to detect a small effect size (Cohen's *d* = 0.25) for between-group difference on the primary outcome if one exists.

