Nonetheless, there are some limitations in our trial. This is a single-center study, and the number of participants in our study is not large. The multi-center study design is expected to obtain a larger sample size in the future. Moreover, the lack of patient blinding may increase bias. Participants in the control group may reduce their participation, which will increase the difficulty of recruiting subjects. The number of interventions in the balanced-enhanced experimental group will be recorded automatically by the “Shoupa” app. Conversely, the actual adherence to the intervention needs to be confirmed and followed up by weekly telephone calls. The “Shoupa” app is expected to strengthen the function of video recording to monitor the training compliance of persons with PD.

Information gained from this project has the potential to influence the clinical decisions of doctors and will provide clear evidence as to whether app-based Tai Chi training should be advocated in people with PD. In conclusion, we expect that the presented app-based Tai Chi training in the patients' home-environment will be effective in balance ability.

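### Baseline LOS is not used as a covariate and the t-test quantity is unstated; one baseline-adjusted model would be more precise at no cost

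*Protocol article*

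**What the plan says.** All analysis rules come from the protocol article, section Statistical Analysis.

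- **Main comparison:** "Repeated measure ANOVA will be used to compare the changes from baseline to 16 weeks among the control group", the basic experimental group and the balanced-enhanced group. No covariate is named. Table 1 has no week-16 assessment, so I read this as the end-of-intervention visit at week 17.
- **Gate:** the balanced-enhanced arm is compared with each of the other two, and these comparisons "will be conducted only if the omnibus F-test statistics indicated that the null hypothesis should be rejected".
- **Pairwise estimate:** an independent-sample t-test ("95% confidence interval) will be used to compare group means"). The sentence does not say which means: changes or follow-up values.
- **Baseline:** "Differences between groups of baseline variables will be tested using the chi-square test" for categorical variables and one-way ANOVA for continuous ones. Table 1 schedules LOS at baseline, week 17 and week 33 for everyone.
- **Attrition:** Sample Size Calculation assumes 15% overall, not split by arm. The Balanced-Enhanced Experimental Group section says "the research team will count the participants who withdrew from the study and the reasons for the withdrawal". The Discussion says "Participants in the control group may reduce their participation" and, in the same sentence, links this to difficulty in recruiting.

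**The concern.** Baseline LOS is likely to be the strongest available predictor of follow-up LOS. A change score uses it with its coefficient fixed at 1. A covariate model estimates the coefficient, and in a randomised trial this is never less precise in large samples. With about 41 participants per arm expected to complete, the unused precision matters.

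The second issue is coherence. The gate tests changes, while the confidence interval that will be reported comes from a separate t-test on an undefined mean. If that is the follow-up mean, a trial can pass the gate on one quantity and report an estimate of another.

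The third issue is conditional. If people with poorer baseline balance left one arm more often than another, both unadjusted completer comparisons would be off target.

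**Working it through.** **Inputs from the document.** 144 participants, 1:1:1, so 48 per arm. With 15% attrition, 48 × 0.85 = 40.8 per arm. The stated target is to "detect a small effect size (Cohen's *d* = 0.25) for between-group difference on the primary outcome", with "Based on sample size calculations (α = 0.05, β = 0.2" as error rates. Sidedness is not stated; I take two-sided.

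**The plan's own figure.** A two-sided, two-arm comparison at d = 0.25 with 80% power needs 252 per arm, which is 756 for three arms before attrition. The stated 144 is therefore not reproduced from the stated d. That is a separate problem; 40.8 per arm is used below only as the size the trial will have.

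**Assumptions.** The outcome SD is 1 at both visits. The correlation r is not in the document and is varied from 0.3 to 0.9.

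**Step 1: the ANOVA is a change-score test.** On a simulated three-arm data set with 41 per arm, the group-by-time F from the two-visit repeated-measures ANOVA and the one-way F on change scores were both 0.7736.

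**Step 2: variance per participant.**
- Follow-up value: 1
- Change score: 2(1 − r)
- Baseline-adjusted: 1 − r²

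The ratio of adjusted to change is (1 − r²)/[2(1 − r)] = (1 + r)/2. The ratio of adjusted to follow-up value is 1 − r².

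**Step 3: numbers.** Power is for one ungated pairwise test at d = 0.25 (in outcome SD) and 40.8 per arm, by the normal approximation Φ(0.25 × √(40.8/2)/√V − 1.96), where V is the variance from step 2.

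| r | V change | V adjusted | Adjusted/change | Power, change | Power, adjusted |
|---|---|---|---|---|---|
| 0.3 | 1.40 | 0.91 | 0.65 | 15.7% | 21.9% |
| 0.5 | 1.00 | 0.75 | 0.75 | 20.3% | 25.6% |
| 0.7 | 0.60 | 0.51 | 0.85 | 30.8% | 35.2% |
| 0.8 | 0.40 | 0.36 | 0.90 | 43.1% | 46.9% |
| 0.9 | 0.20 | 0.19 | 0.95 | 71.4% | 73.6% |

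A t-test on follow-up values has V = 1 and 20.3% power at every r, so the adjusted V column is also its variance ratio (0.91 down to 0.19).

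**Step 4: gate and estimate.** This applies only if the t-tests use follow-up values. Simulating 41 per arm, no dropout, a Tai Chi effect of 0.28 SD and r of 0.5 to 0.8, neither Tai Chi t-test was significant in roughly half of the trials that passed the change-score gate.

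**Step 5: dropout.** Suppose control completers have a mean baseline δ SD above that of all randomised controls, dropout depends only on arm and baseline, and the Tai Chi arm loses people at random. Completers' follow-up mean is then shifted by rδ and their change by (r − 1)δ. The Tai Chi minus control bias is therefore −rδ for follow-up values, +(1 − r)δ for changes, and 0 after baseline adjustment.

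A 5,000-run simulation used a true effect of 0.25, about a quarter of controls leaving (more often at poor baseline) and 5% random loss in the Tai Chi arm:

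| r | Change | Follow-up value | Adjusted |
|---|---|---|---|
| 0.5 | 0.355 | 0.142 | 0.248 |
| 0.7 | 0.313 | 0.101 | 0.249 |

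These match the formulas at δ ≈ 0.21: for example, at r = 0.7, 0.3 × 0.21 = 0.063 and 0.7 × 0.21 = 0.147.

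With 15% random dropout in both arms, all three estimates centre on about 0.25 and only the standard error, √(2V/40.8), differs. For change against adjusted it is 0.221 against 0.192 at r = 0.5, and 0.171 against 0.158 at r = 0.7.

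**The case against.** The strongest reply is that a change-score comparison in a randomised trial is valid and already uses baseline, so this is an efficiency choice and not an error. The gain against change scores is also modest if r is high: 5% of variance at r = 0.9. Both points stand, and they are why this is put as an improvement.

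Four stronger readings are tempting, and the document does not support them:

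- **That the plan ignores baseline.** It omits baseline only as a covariate; the ANOVA compares changes from it.
- **That everyone without a post-baseline visit is dropped.** No exclusion rule, analysis set or missing-data rule is stated. A reader might infer complete-case analysis from how classical repeated-measures ANOVA works, but such rules commonly sit in an analysis plan, which is not shown here. A mixed model with baseline as a covariate would also omit a person with no follow-up value.
- **That the protocol expects differential dropout.** The Discussion says only "Participants in the control group may reduce their participation" and gives recruitment difficulty as the consequence. Attrition is a single 15%. Unequal dropout is plausible with controls held at a registration screen, but it is not predicted.
- **That the t-tests use follow-up values.** They may be on mean changes. In that case gate and estimate agree, and the 1 − r² ratios and the negative bias do not apply.

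The dropout scenario also favours adjustment by construction. If leaving depended on the unobserved outcome, the adjusted estimate would be biased too. Finally, the baseline significance tests adjust nothing, but as written they do not alter the primary analysis either; they are a reporting matter.

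**Conclusion.** The point holds as a precision and clarity issue. The planned comparison omits a covariate measured in everyone, and the quantity behind the reported confidence intervals is not defined.

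Against change scores, adjustment leaves 65% to 95% of the variance, a saving of 35% down to 5% in required sample size for r from 0.3 to 0.9. Against follow-up values it leaves 91% down to 19%. These figures assume equal SDs at the two visits and an r that the document does not give, and they neglect the single degree of freedom spent on the covariate.

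The bias is conditional on dropout that differs by arm and depends on baseline balance. Its size in the illustration comes from assumed rates, not from the protocol.

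Adjustment does not rescue the sample size: at d = 0.25 power stays below 80% across the whole range of r.

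**What to change.** Replace the repeated-measures ANOVA and separate t-tests with one baseline-adjusted model for each LOS measure. Either of these would do:

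- ANCOVA of the week-17 value on arm and baseline value.
- A linear mixed model over weeks 17 and 33 with arm-by-visit terms, and baseline either as a covariate or as a first visit with its mean constrained equal across arms. The constrained version is the one that keeps participants with no follow-up value; the covariate version mainly helps those with one of the two follow-up visits.

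Take the two planned pairwise differences and their 95% confidence intervals at week 17 from that same model. If the omnibus gate is kept, test it there as well.

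Suggested text: *For each LOS measure, arms will be compared at week 17 in a model adjusting for the baseline value of that measure. Differences between the balanced-enhanced arm and each other arm, with 95% confidence intervals, will be estimated from this model.*

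The cost is a few lines of text and standard code in R, which the protocol already names. No new data, visits or participants are needed. The mismatch between d = 0.25 and 144 must be resolved separately.

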### Randomization and Allocation Concealment and Blinding

Randomization will be achieved through a random sequence table generated by a computer (Excel software; Microsoft). The subject's randomization will be carried out by a researcher who will not enroll the participants, assign them to their groups, or perform outcome measurements. The researcher will conceal the distribution in an opaque envelope, which can only be opened after the subject has completed the baseline assessment. The subjects will be randomly assigned to three groups (allocation ratio 1:1:1). Only the researcher responsible for guiding the use of the app can know how the participants are allocated. The researcher responsible for the follow-up reviews will be blinded to the distribution at any time during the data collection period. Moreover, the group assignment will be blinded to the assessors and data analysts.

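### The omnibus F gate is valid error control, but as written it withholds both Tai Chi contrasts whenever F is not significant, and the sample size section does not say which test its 80% power describes

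*Protocol article*

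**What the plan says.** The Statistical Analysis section of the protocol article starts from a three-group analysis: "Repeated measure ANOVA will be used to compare the changes from baseline to 16 weeks among the control group" and the two app groups. Pairwise comparisons of the Tai Chi group with each of the other two groups then "will be conducted only if the omnibus F-test statistics indicated that the null hypothesis should be rejected". The next sentence gives an independent-samples t-test with a 95% confidence interval for comparing group means. No other multiplicity adjustment is stated.

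The Sample Size Calculation section discusses effects contrast by contrast. It quotes d = 0.28 from an earlier Tai Chi trial and says that "a similar effect size difference is anticipated between the balanced-enhanced experimental condition and the control condition". It adds: "A smaller effect size difference is anticipated between the balanced-enhanced experimental condition and the basic experimental condition", and gives this as the reason for a larger sample. With α set at 0.05 and β at 0.2, it concludes that "a total sample of 144 (assuming 15% attrition) will be sufficient". The target effect there is a Cohen's d of 0.25 between groups. The section does not name the test to which α and β apply, and it does not mention the gate.

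**The concern.** The two comparisons that answer the trial's question are fixed in advance, yet neither is carried out unless a non-directed test with 2 degrees of freedom succeeds first. That test also responds to the difference between basic app and control, which is not one of the planned contrasts. If the basic-app mean lies between the other two, as the sample size section anticipates, Tai Chi versus control can be significant by itself while F is not.

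Two consequences follow. A trial with a non-significant F would, on the plain wording, publish no estimate or interval for Tai Chi against either comparator, although those are the figures that readers and later meta-analyses need. And a reader who takes the 80% as the chance of showing Tai Chi better than control cannot tell whether the figure allows for the gate.

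**Working it through.** **Inputs from the document.** Total 144, allocated 1:1:1, so 48 per arm. With 15% attrition, 144 × 0.85 = 122.4, or about 41 per arm. α = 0.05 (taken as two-sided, since the side is not stated) and β = 0.2. Effects d = 0.25 and 0.28.

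**Assumptions, not in the document.** Normal outcome, unit SD, equal variances. The basic-app mean is varied from the control mean to the Tai Chi mean, because its position is not quantified.

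**1. The plan's own figure.** For one pairwise contrast at d = 0.25:

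n per arm = 2(1.96 + 0.84)² / 0.25² ≈ 252; 252 / 0.85 ≈ 297; 3 × 297 = 891.

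The stated 144 is not reproduced. Conversely, the noncentrality is d√(n/2) = 0.25 × √(41/2) = 1.13, which gives 20.1% power at 41 per arm. At 48 per arm power is 22.8%. At d = 0.28 the figures are 24.0% and 27.4%.

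One route does come close to 144. It reads 0.25 as Cohen's f in the between-groups F test of a repeated measures ANOVA with an assumed 2 measurements and correlation 0.5. The noncentrality is then 120 × 0.25² × 2 / 1.5 = 10, power is 80.5% at N = 120, and 120 / 0.85 gives 142, or 144 in three equal groups. This contradicts the stated Cohen's d and needs inputs that the article does not give.

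**2. Effect of the gate at the plan's effects.** Simulation (1,000,000 trials per row): three-arm F at 5%, then a two-sided 5% t-test of Tai Chi versus control.

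| n per arm | d | Basic-app mean | F significant | Ungated | Gated |
|---|---|---|---|---|---|
| 41 | 0.25 | = control | 19.4% | 20.1% | 13.6% |
| 41 | 0.25 | midway | 15.6% | 20.1% | 12.7% |
| 41 | 0.28 | = control | 23.4% | 24.0% | 16.9% |
| 41 | 0.28 | midway | 18.5% | 24.1% | 15.7% |
| 48 | 0.25 | = control | 22.2% | 22.9% | 15.9% |
| 48 | 0.25 | midway | 17.5% | 22.8% | 14.7% |
| 48 | 0.28 | = control | 27.0% | 27.5% | 19.9% |
| 48 | 0.28 | midway | 21.1% | 27.4% | 18.2% |

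Placing the basic-app mean at the Tai Chi mean gives almost the same figures as placing it at control. If 0.28 and 0.25 are taken as the two anticipated effects (means 0, 0.03, 0.28), 41 per arm gives F significant in 21.5%, ungated 24.0% and gated 16.4%.

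So F is not significant in 73% to 84% of trials, and the gate costs 6.5 to 9.2 points. The gap between 80% and the ungated 20% to 27% is 53 to 60 points.

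**3. Effect of the gate if the contrast did have 80% power.** That needs d of about 0.63 at 41 per arm, which is an illustration and not a figure from the plan. With pooled variance, ungated power of 80.8% falls to 76.6% (basic = control), 71.2% (basic one third of the way) and 70.3% (midway). The loss is 4 to 11 points.

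**4. Error control.** With all three means equal, the chance of a false claim on either Tai Chi contrast is 4.1% with the gate and 9.1% without it. If only one pair is equal, only one true null can be rejected, by a single 5% t-test.

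**5. A fixed order instead (Tai Chi–control, then Tai Chi–basic).** This keeps full Tai Chi–control power. Tai Chi–basic power at 41 per arm, gate versus fixed order, Tai Chi–control d = 0.63 unless stated:
- basic = control: 76.6% versus 69.9%
- one third of the way: 44.6% versus 43.5%
- midway: 28.1% versus 27.9%
- basic 0.15 SD below control: 90.6% versus 78.2% (here the gate costs Tai Chi–control only 1.4 points)
- means 0, 0.03, 0.28: 14.1% versus 10.1%

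**The case against.** The strongest reply is that the gate is a recognised procedure (Fisher's protected LSD) and the only multiplicity control stated for the two contrasts. Other procedures that treat them symmetrically cost about as much. If ungated power were 80%, Dunnett would give 72.4% and Bonferroni 70.9% for Tai Chi versus control, against 69.6% to 75.7% with the gate. This stands, and it rules out calling the gate a mistake.

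A reader might go further and infer that the contrasts should be tested in a fixed order without the gate. The documents do not support that as a correction. The sample size section ranks the contrasts by expected size, not importance, and makes the smaller effect its reason for the larger sample. The Discussion singles out whether adding Tai Chi improves balance, which is most directly the comparison with the basic app. A fixed order would put that comparison second and lower its power.

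A reader might also infer that the 80% ignores the gate. That cannot be shown. The powered test is not named, and the only route found to about 144 powers an omnibus F, a test of the same kind as the gate. Even on that route, Tai Chi versus control has 77% to 88% power ungated and 72% to 80% gated, so the 80% would still not describe that contrast.

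Lastly, the t-test sentence with its 95% confidence interval could be read as standing outside the gate, and a fuller analysis plan may say so. On the plain order of the text, however, it names the method for the gated comparisons, and the gate itself is a firm rule rather than a detail left open.

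**Conclusion.** The gate is valid and may stay. What does not stand is using it to decide whether the two planned contrasts are computed at all, and quoting 80% power without saying for which test.

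At the plan's effects, the rule as written leaves both contrasts without an estimate in about 73% to 84% of trials. Power for a significant Tai Chi versus control result is about 13% to 20% under the plan's procedure and 20% to 27% without the gate. The sample size inputs account for most of the shortfall, and the gate for the last 6 to 9 points.

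These figures assume 41 to 48 evaluable per arm, two-sided 5% tests, equal variances, d read as a standardised pairwise difference in the analysed outcome, and a basic-app mean between the other two. If basic app were worse than control, the gate would cost Tai Chi versus control less.

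**What to change.** 1. **Statistical Analysis.** State that both Tai Chi contrasts are estimated and reported with 95% confidence intervals whatever the omnibus F shows, and that F decides only whether a significance claim may be made. This is one sentence. It needs no new data and leaves the error control unchanged. The intervals are not multiplicity-adjusted and should be labelled so.

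2. **Sample Size Calculation.** Name the test to which α = 0.05 and β = 0.2 refer, say whether 0.25 is d or f, and restate power, or the detectable effect, for Tai Chi versus control under the gated procedure, with the assumed basic-app mean. This costs a short recalculation. It will probably show that 144 participants give far less than 80% power at d = 0.25.

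3. **Optional.** The sponsor may replace the gate with a fixed order if Tai Chi versus control is the more important question. This restores 4 to 11 points for that contrast when its ungated power is about 80%, and 6 to 9 points at the plan's effects. It takes about 0 to 7 points from Tai Chi versus basic app if basic is at or above control, and about 12 if basic is 0.15 SD below it. The choice should be made and recorded before unblinding.
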